## Results

This study received no specific grant from any funding agency in public, commercial, or not-for-profit sectors. Recruitment began in October 2021 at Portimão Hospital and Alvor Hospital, in June 2022 at Faro Hospital and São Sebastião Hospital, and in October 2022 at Fernando Fonseca Hospital. The deadline for the end of the recruitment period in all centers was December 2023. The preliminary study results will be published in a peer-reviewed international medical journal after October 2023. The study timeline is shown in Figure 2. This study is included as part of the first author’s (LP) PhD thesis. The initial study results were presented at the PhD interview in November 2023. We aim to publish the study in an indexed scientific journal and present the results at national and international congresses.

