**Methods:**

Using a consecutive nonrandom sampling technique, we will conduct a prospective cohort multicenter observational study in 5 Portuguese hospitals. Symptomatic adult patients with previous COVID-19 attending follow-up consultations will be enrolled. We will include patients who had mild, moderate, and severe acute disease. We will assess clinical outcomes related to COVID-19, including the type of respiratory support such as high-flow nasal cannula, noninvasive ventilation, and invasive mechanical ventilation. The exclusion criteria will include previous severe psychiatric disorders confirmed by a psychiatrist; refusal or inability to respond to the questionnaire; concomitant neurological disorder; persistent fatigue symptoms during the 6 months before infection; and the need for invasive mechanical ventilation during COVID-19 infection due to a high prevalence of postintensive care syndrome. Our primary outcome is the prevalence of fatigue in patients with post–COVID-19 depression and/or anxiety, as measured by the Chalder Fatigue Scale (CFQ-11) and the Hospital Anxiety and Depression Scale (HADS). The secondary outcomes will include an assessment of health-related quality of life via the EQ-5D questionnaire and an exploration of the prevalence of symptoms of posttraumatic stress disorder (PTSD) using the 14-item Posttraumatic Stress Scale (PTSS-14). We will also examine the association between mental health symptoms and the severity of acute COVID-19. The post–COVID-19 data will be collected at least 6 months after the positive test and no longer than 9 months during the clinical appointment.

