### Data Collection

Data collection will take place during appointments at the long COVID follow-up clinics in all participating hospitals. Qualified clinical study staff will gather the data using a clinical research form (CRF) (Multimedia Appendix 1). These individuals comprise health care professionals, such as nurses, clinical research coordinators, and health care experts who have received appropriate training and have the necessary expertise to conduct data collection and assessments in a clinical research setting. Their training ensures adherence to research protocols and ethical guidelines, guaranteeing accurate and consistent data gathering during clinical appointments. Two months after hospital discharge, we will mail all patients a letter offering a follow-up consultation in the outpatient clinic. Patients who agree to attend will be offered 2 appointments, consisting of an anamnesis and a physical examination, and given several self-administered tests in the waiting room. We will allocate 15 minutes for the questionnaire completion in the waiting room. In the first visit (T1, 3 months), the following data will be additionally collected: demographic characteristics like age, sex, and BMI (kg/m^2^); each participant’s medical history, such as the date of the first positive COVID-19 test (PCR or antigen) and smoking, alcohol, and drug consumption status; comorbidities and usual medication intake; and screening of symptoms and severity of the acute disease. Data collection in the second visit (T2, 6 months) will include post–COVID-19 symptoms, the Chalder Fatigue Scale [26] (CFQ-11), the Hospital Anxiety and Depression Scale (HADS) [27], the 14-item Posttraumatic Stress Scale (PTSS-14) adapted to COVID-19, and the EQ-5D [28] questionnaire.

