The 5 phases of the statistical analyses carried out in this study.Phase 1: Characterization of the patient sample1.1. Sociodemographic analysis of the variables collected at T1 and the variables from the surveyed instruments at T2. This involves descriptive analysis, both univariate and bivariate, which will be differentiated by:1.1.1. Quantitative variables: mean and SD, coefficient of variation, and median and IQR1.1.2. Qualitative variables (nominal and ordinal categorical): analysis of distributions through absolute and relative frequencies, including absolute and relative accumulated frequencies1.1.3. Quantitative variables will be reported alongside appropriate tests for normal distribution to ensure the accuracy and validity of our statistical analyses.1.2. Bivariate and descriptive analysis using 2D tables will be calculated for all qualitative variables belonging to T1 with all instrument scores collected at T2: Chalder Fatigue Scale (CFQ-11), Hospital Anxiety and Depression Scale (HADS), 14-item Posttraumatic Stress Scale (PTSS-14) adapted to COVID -19, and EQ- 5D plus recorded COVID-19 symptoms. The previous points will be reiterated in this bivariate context, utilizing the computational aid of split->file categorical variables in situations where one variable is metric and the other is categorical.1.3. Internal consistency and reliability analysis of the T2 instruments: calculation of the Cronbach alpha (general and partial) for all ordinal items and item subgroups differentiated by the subscales defined by the respective authorsPhase 2: Determination of fatigue incidence caused by long COVID and its relationship with T1 and T2 variables2.1. Procedures for determining fatigue cutoff points in this cohort of patients:2.1.1. Bivariate analysis using optimal binning procedures for categorical variables (age class, sex, and BMI) with the total fatigue score, as well as partial scores of physical and psychological fatigue2.1.2. Multivariate analysis by constructing models in the format of decision trees via the CHAID (chi-square automatic interaction detection) algorithm [41], with total and partial fatigue scores as dependent variables2.2. Inferential analysis based on variables resulting from 2.1.1 and/or 2.1.2, considering the complexity of variables in T1 and T2:2.2.1. (1) Chi-Square tests to capture the association of categorical variables; (2) Shapiro-Wilk tests to verify the distribution of quantitative variables; (3) tests for comparing 2 or more population means: parametric analysis of variance (ANOVA) test and nonparametric (Kruskal-Wallis) test; and (4) correlation tests (Spearman or Pearson) to verify the degree of association between T2 instrument scalesPhase 3: Determination of patient groups based on fatigue differentiation3.1. Conducting classification analysis using clustering techniques, specifically the 2-step cluster analysis, to explore variables with greater power in differentiating groups of patientsPhase 4: Exploration of the best combination of T1 and T2 variables capable of discriminating patient fatigue levels through a discriminant multivariate analysisPhase 5: Investigation of the association between phase 3 groups and all T2 instrument scales using chi-square association tests

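### The severity versus mental-symptom comparison is planned only as pooled, unadjusted tables, although recruitment was staggered over 26 months and the infection date is recorded

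*Protocol article*

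**What the plan says.** **The aim.** The Abstract (Methods) states: "We will also examine the association between mental health symptoms and the severity of acute COVID-19". The section on the association of mental illness symptoms with acute severity defines the WHO severity categories but names no analysis.

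**The data.** Under Data Collection, the first visit (T1) records the date of the first positive test and "screening of symptoms and severity of the acute disease". HADS and PTSS-14 are collected at the second visit (T2).

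**The analysis.** Textbox 2, phase 1.2, reads: "Bivariate and descriptive analysis using 2D tables will be calculated for all qualitative variables belonging to T1 with all instrument scores collected at T2". Severity is a categorical T1 variable, so it falls under this step. Step 2.2.1 lists chi-square, ANOVA, Kruskal-Wallis and correlation tests, without covariates.

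**The calendar.** Results gives the first four openings: "Recruitment began in October 2021 at Portimão Hospital and Alvor Hospital, in June 2022 at Faro Hospital and São Sebastião Hospital". The fifth hospital joined four months after the second pair. On closing, the same section says: "The deadline for the end of the recruitment period in all centers was December 2023".

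**The concern.** A pooled table of severity against symptoms treats all patients as if they came from one period. They did not. The hospitals opened in three waves over a year, and the declared end of the pandemic that the Introduction cites (May 2023) falls inside the recruitment window. The hospitals are a mix of one private and four public, and the Exclusion Criteria section says the inclusion criteria will be reviewed regularly. So both the severity mix and the general level of distress could have changed over time or differed between hospitals.

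If both changed, severity and symptoms would be associated in the pooled data even if severity had no effect within any period. A reader of the crude table could not separate a severity effect from a period effect. Because the hospitals entered at different times, a difference between hospitals could likewise be one of period.

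**Working it through.** The article gives no duration, sample size or power for this comparison, so there is no stated figure to reproduce. The check has three parts.

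**1. Calendar arithmetic (dates from Results)**
- Opening span: October 2021 to October 2022 = 12 months.
- Recruitment: October 2021 to December 2023 = 26 months (27 if both end months are counted).
- Recruitment per hospital: 26 months (two hospitals), 18 (two) and 14 (one).
- Index infections, if entry is a fixed 6 months after the test: April 2021 to June 2023 = 26 months. With entry at 3 months (T1) the window moves to July 2021 to September 2023, also 26 months.
- If entry may fall 6 to 9 months after the test, as in the Abstract's window: January 2021 to June 2023 = 29 months.

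Every hospital recruited for at least 14 months, so adjusting for hospital alone would not remove a period effect.

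**2. What each analysis step has as its target (Textbox 2)**
- 1.2: T1 categorical variables against T2 scores, pooled. This includes severity.
- 2.1.1 and 2.1.2 (optimal binning, CHAID): fatigue scores.
- 2.2.1: unadjusted tests, introduced as building on the variables from 2.1.
- 3: clusters of patients based on fatigue differentiation.
- 4: discriminant analysis of fatigue levels.
- 5: chi-square tests of the phase 3 groups against the T2 scales.

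No multivariable step has HADS or PTSS-14 as its outcome, and no step names infection date, period or hospital.

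**3. Size of the possible bias (assumed figures)**
Take two equal periods with severe shares s1, s2 and symptom prevalences m1, m2, and no severity effect within either period. Then
- severe patients with symptoms: a = (s1·m1 + s2·m2)/(s1 + s2)
- other patients with symptoms: b = [(1−s1)·m1 + (1−s2)·m2]/[(1−s1) + (1−s2)]
- crude OR = [a/(1−a)]/[b/(1−b)]
- z = |a−b|/√[p(1−p)(1/n1 + 1/n2)], where p is the overall prevalence and n1, n2 are the numbers of severe and other patients; rejection rate = Φ(z−1.96) + Φ(−z−1.96)

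Example: severe 50% then 20%, symptoms 60% then 40%, N = 200. Then a = (0.30 + 0.08)/0.70 = 0.543 and b = (0.30 + 0.32)/1.30 = 0.477, so the OR is 1.30. With n1 = 70, n2 = 130 and p = 0.50, z = 0.066/0.074 = 0.89 and the rejection rate is 14.4%.

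| Severe share | Symptoms | N | Crude OR | Test rejects |
|---|---|---|---|---|
| either row constant | | 200 | 1.00 | 5.0% |
| 50% → 40% | 55% → 45% | 200 | 1.04 | 5.2% |
| 40% → 25% | 50% → 40% | 187 | 1.07 | 6% |
| 50% → 30% | 60% → 40% | 200 | 1.18 | 8.9% |
| 50% → 20% | 60% → 40% | 200 | 1.30 | 14.4% |
| 60% → 20% | 60% → 35% | 187 | 1.52 | 28–29% |
| 60% → 20% | 65% → 35% | 200 | 1.65 | 41.0% |
| 60% → 15% | 60% → 30% | 187 | 1.79 | 48–50% |

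The first row means that severity or symptoms stays the same over time. N = 200 is the article's required sample, and those rows use the normal approximation. N = 187 is 250 less 25% loss, and those rows were simulated; there, a test stratified by the two periods rejected in about 5% of datasets.

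**The case against.** - **The severity test is inferred.** No phase names severity against mental symptoms. Phase 1.2 belongs to the description of the sample, and 2.2.1 is tied to the fatigue steps. This stands: what can be said is that the only step that reaches the aim is pooled and bivariate. The rejection rates above describe a test that the article may or may not intend.
- **Covariates are commonly left to the full analysis plan.** This would settle the matter if the article had merely been silent. It sets out five phases with named methods, however, and gives every multivariable step to fatigue. The point is about that allocation.
- **No drift is shown.** This stands in full. The article has no figure by period or hospital, and the bias needs both severity and symptoms to shift. Eligibility also narrows the mix: all patients have persistent symptoms, and ventilated patients and those with a prior psychiatric diagnosis are excluded.
- **Period is only one possible covariate.** True; age, sex and comorbidities are also unnamed for this comparison. Period and hospital are singled out because the staggered openings build their overlap into the design.
- **Stratification would be sparse.** Correct. With half-year periods and a fixed 6-month lag, crossing period with hospital gives 2×5 + 2×4 + 3 = 21 strata, or 187/21 ≈ 9 patients each, spread over up to four severity categories.

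A reader might infer that the severity result will be a calendar artefact, or that its false-positive rate is 14% to 50%. The documents support neither; those rates follow only from the large assumed shifts. Nor should one picture infections balanced around the end-of-pandemic declaration: on the 6-month reading, only May and June 2023 come after it.

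**Conclusion.** The point holds as a limited one. For a declared secondary aim, the analysis set out is crude and pooled, while recruitment was staggered and long enough for hospital and period to be partly confounded. Whether this biases the result cannot be known from the article. Under assumed two-period shifts with no true effect, the crude odds ratio is 1.00 if either variable is stable, about 1.04 to 1.18 for modest shifts, and about 1.3 to 1.8 for large ones. The dates and the allocation of methods come from the article; all period-specific percentages are assumptions. The primary fatigue question is not at issue here. The change is worth making because it is cheap and uses data already recorded, not because bias has been demonstrated.

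**What to change.** Amend Textbox 2 for the severity aim as follows:

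- Keep the two-way tables of phase 1.2 as description.
- Base the severity conclusion on a regression of HADS and PTSS-14 scores on severity category. Include as covariates the calendar period of the index infection (a few broad categories, or a smooth term, from the date of first positive test) and hospital.
- Report the severity mix by period and by hospital, so that readers can see whether drift occurred.
- Do not use Mantel-Haenszel strata that cross period with hospital; they would be too sparse.

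**Cost.** A short addition to the text, and no new data, visits or patients; it can be done at the analysis stage. It adds two multi-level factors, not one covariate: five hospitals take 4 degrees of freedom, and period takes 2 with three categories or 4 with five half-years, so 6 to 8 in all. Intervals will be slightly wider, and because period and hospital overlap, their separate effects will be imprecisely estimated.

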**Figure 2 figure2:**
[figure not shown]
Study timeline.

We plan to enroll 250 participants, including 100 with adverse mental health symptoms and 100 without, to explore the intricate relationship between adverse mental health symptoms and both physical and psychological fatigue in individuals recovering from long COVID. Preliminary analyses indicate a compelling connection, wherein patients who report heightened levels of depression and anxiety also tend to experience increased fatigue. These findings underscore the importance of considering mental health as a pivotal factor in understanding the enduring impact of COVID-19 beyond the acute phase. In addition to depression and anxiety, our study explores the persistence of PTSD symptoms in a subset of participants. Initial results suggest that, even after recovery from the acute phase of the infection, a proportion of individuals continue to grapple with the psychological repercussions of the virus. This observation aligns with emerging evidence suggesting a prolonged psychological impact of COVID-19, emphasizing the need for comprehensive mental health support for patients after contracting COVID-19. The identified links between mental health symptoms and fatigue have broad implications for the holistic care of this patient population. Understanding these connections can guide targeted interventions, emphasizing the importance of addressing mental well-being alongside physical recovery. As we delve deeper into the data and conduct further analyses, a more nuanced understanding of these relationships will emerge, informing future health care strategies and interventions.

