### Recruitment

Our study will be conducted in 1 private and 4 public Portuguese hospitals that have established follow-up post–COVID-19 medical consultations. Patients who meet the eligibility criteria will be invited to participate in the study at the end of their appointments in the follow-up clinics. This study will be conducted using a consecutive, nonrandom sampling technique.

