
### Power and Sample Size

We plan to conduct a prospective multicentric observational study to investigate the prevalence and severity of mental illness symptoms and fatigue in individuals with long COVID. Based on previous studies and expert opinion, we expect the prevalence of fatigue and mental symptoms in this population to be around 50% [42,43]. We aim to detect a minimum effect size of 0.2 with a power of 80% and a significance level of *P=.*05.

Using these assumptions, we performed a sample size power analysis using a 2-sample *t* test. We found that a total sample size of 200 participants (100 with adverse mental health symptoms and 100 without) would be required to detect the minimum effect size of 0.2 with 80% power and a significance level of *P=*.05. The required sample size was calculated using an a priori power analysis with an online calculator [44]. To compensate for a projected 25% loss to follow-up, we aimed for 250 participants.

We plan to recruit participants from multiple hospitals and primary care centers across Portugal, focusing on individuals who have been diagnosed with long COVID and are experiencing mental illness symptoms and/or fatigue. Recruitment will be closely monitored throughout the study to assess the pace at which participants are enrolled. The need for sample size adjustment will be determined based on the observed recruitment rates and the accumulating data. We plan to conduct an interim analysis after the recruitment of the first 100 patients.

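### Consecutive sampling, a recruitment focus on mental symptoms and/or fatigue, and an enrolled composition of 100 with and 100 without mental symptoms are all stated and not reconciled

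*Protocol article*

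**What the plan says.** - **Sampling.** Methods, Recruitment: "This study will be conducted using a consecutive, nonrandom sampling technique". The Abstract says the same. Patients are invited at the end of a follow-up clinic appointment.
- **Aim.** Power and Sample Size describes a study "to investigate the prevalence and severity of mental illness symptoms and fatigue in individuals with long COVID", with both expected at around 50%.
- **Required size.** Same section: "a total sample size of 200 participants (100 with adverse mental health symptoms and 100 without) would be required". This is raised to 250 for a projected 25% loss to follow-up.
- **Recruitment focus.** Same section: recruitment concentrates on people with diagnosed long COVID who "are experiencing mental illness symptoms and/or fatigue".
- **Composition.** Results, paragraph after Figure 2: "We plan to enroll 250 participants, including 100 with adverse mental health symptoms and 100 without".
- **When mental symptoms are measured.** Data Collection: "Data collection in the second visit (T2, 6 months) will include post–COVID-19 symptoms, the Chalder Fatigue Scale", followed by the HADS, PTSS-14 and EQ-5D. The list introduced by "In the first visit (T1, 3 months), the following data will be additionally collected" does not contain the HADS.
- **When patients enter.** Inclusion Criteria require at least 6 months since diagnosis, yet Data Collection describes a 3-month visit at which study data are gathered.
- **Primary outcome.** Abstract: the prevalence of fatigue in patients with depression and/or anxiety after COVID-19.

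**The concern.** Under consecutive sampling the numbers with and without mental symptoms are whatever the clinics yield. A stated composition of the enrolled sample is a different rule, and a focus on people with either trait is a third. The three lead to different estimates.

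The exposed overall estimates are the prevalence of mental symptoms, the prevalence of fatigue and, as a secondary outcome, the prevalence of PTSD symptoms. Each is interpretable for the clinic population only if nobody was taken or passed over because of mental-symptom or fatigue status. A reader of the final report could not tell from this article which rule produced the sample.

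The 100/100 figure also underlies the power statement. If it is an expectation and not a design feature, its dependence on the 50% assumption and on the stated loss should be visible.

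**Working it through.** **Inputs from the article:** 200 required (100 + 100), 250 enrolled, 25% loss, expected prevalence about 50%, effect size 0.2, 80% power, alpha 0.05. **Assumed here:** true mental-symptom prevalence of 30%, 40% or 50%; fatigue 70% with and 40% without mental symptoms; a difference of 0.4 SD for the power comparison; two-sided testing.

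**1. The article's own figures.** 200 × 1.25 = 250, so the 50 beyond 100 + 100 match the loss allowance. The 100 per group does not follow from an effect size of 0.2 in a two-sample t test: n = 2(1.96 + 0.84)²/0.2² ≈ 393 per group. That is a separate matter. It is noted only because it explains the use of 0.4 SD below, which is about what 100 per group can detect.

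**2. If the composition were followed at enrolment.** Filling the groups 1:1 makes observed mental-symptom prevalence 50%:
- truth 30%: 50 − 30 = +20 points
- truth 40%: 50 − 40 = +10 points
- truth 50%: 0

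Read more loosely, as at least 100 of each among 250, the observed figure must lie between 100/250 = 40% and 150/250 = 60%. A truth of 30% is then still overstated by at least 10 points.

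Overall fatigue at a true mental-symptom prevalence of 30%: 0.3 × 0.70 + 0.7 × 0.40 = 49%. In a 1:1 sample: (0.70 + 0.40)/2 = 55%. The within-group rates of 70% and 40% are the same in both. PTSD-symptom prevalence behaves the same way if it differs between groups.

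**3. If sampling is consecutive.** Evaluable after loss: 250 × 0.75 = 187.5, about 187. Since 187 < 200, 100 + 100 evaluable cannot be reached at any prevalence. Expected splits and normal-approximation power, Φ(0.4·√(n₁n₂/(n₁+n₂)) − 1.96):

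| True prevalence | Split of 200 | Power | Split of about 187 | Power |
|---|---|---|---|---|
| 50% | 100/100 | 0.81 | 94/94 | 0.78 |
| 40% | 80/120 | 0.79 | 75/112 | 0.76 |
| 30% | 60/140 | 0.74 | 56/131 | 0.71 |

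If all 250 were scored with no loss, the binomial chance of at least 100 in each group, P(100 ≤ X ≤ 150), is 99.9% at 50%, 52% at 40% and 0.05% at 30%.

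**4. Point of enrolment.** The HADS is listed only at T2. If patients enter before T2, their group is unknown at entry and no composition can be set then. If they enter at the T2 visit, which Recruitment and Inclusion Criteria allow, selection on the HADS becomes feasible. The article does not say which applies.

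**5. The recruitment focus.** Applied strictly, admitting only people with mental symptoms or fatigue would mean that every participant without mental symptoms has fatigue. That would undermine the comparison in Research Question 1. The focus does not appear among the inclusion criteria, so strict application is not established.

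**The case against.** The strongest reply is that no quota exists. The 100/100 comes from the power calculation, next to an expected prevalence of around 50%, and the Results section repeats it loosely. No cap, HADS screen or rule to keep enrolling until a group fills appears anywhere, and the extra 50 are accounted for by the loss allowance. All of this stands, and it makes the expected-split reading the likely one. It does not remove the conflict, because the Results sentence is worded as a composition of those enrolled, and the expected split of 250 at 50% would be 125/125.

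Three stronger readings are tempting, and the documents do not support them:
- *The 100/100 split cannot be enrolled.* Entry at the 6-month visit is possible, and at 50% prevalence 250 scored patients almost always include 100 of each without any selection. What fails is 100 + 100 evaluable after the stated loss.
- *Fifty patients belong to neither group.* They are the loss allowance.
- *The primary outcome is biased by the split.* It is conditional on mental-symptom status, so a quota on that status alone leaves it unchanged.

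It is also fair to say that unequal splits cost little power and that the 30% and 40% scenarios are not in the article.

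**Conclusion.** The inconsistency is real: three statements about recruitment stand side by side, and only one of them supports the prevalence aim. The consequence is conditional. The 10- to 20-point error in mental-symptom prevalence and the 6-point shift in overall fatigue arise only if the composition was actually enforced, and they rest on the assumed true prevalences and fatigue rates. Without enforcement, what remains is a group-size statement that does not agree with the article's own 25% loss, with a modest effect on power: 0.81 to 0.78 at 50% prevalence and 0.71 at 30%, for an assumed 0.4 SD. The and/or wording is the clearest selection language in the text and, if acted on, the larger threat to the between-group comparison. The point should be corrected, as a matter of reconciling text; it does not show that the sample was in fact selected.

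**What to change.** 1. In Power and Sample Size and in Results, stop presenting 100 with and 100 without as the make-up of the enrolled sample. Give an expected evaluable split at 50% prevalence that agrees with the stated loss, and say that the actual split will depend on observed prevalence.
2. State that enrolment is consecutive among eligible patients, with no selection or quota by mental-symptom or fatigue status, if that is what was done. Remove the and/or focus or reconcile it with the inclusion criteria.
3. State the point of enrolment relative to the 3-month and 6-month visits.
4. Report overall prevalences of mental symptoms, fatigue and PTSD symptoms from the full consecutive sample.
5. If a quota was in fact used, describe it and do not present the overall prevalences as estimates for the clinic population.

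The cost is a few sentences. The stated group sizes and precision become slightly less favourable. No data collection changes.
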